#### Secondary analysis

2.13.3

To limit multiplicity and reduce type I error inflation, secondary analyses are structured into predefined parameter families.

Additional VET Parameters: CFT, A5, A10, MCF, *α*-angle, lysis time, maximum lysisDescriptive Spearman correlations with Anti-XaMixed-effects regression models to explore surrogate potentialStandard Laboratory Assays: INR, aPTT, fibrinogen, platelet count, antithrombin, bilirubin, triglycerides, albuminPartial correlationsMultivariable mixed-effects regressionStandardized *β*-coefficients with 95% confidence intervalsChange in explained variance (Δ*R*^2^)Advanced Haemostatic Markers: FVIII, FXIII, thrombin generation parameters, PAP, PAI-1, TFPI, TATDescriptive correlation analysesComparative interpretation of effect sizes

False discovery rate correction using the Benjamini–Hochberg procedure will be applied within each predefined parameter family.

All baseline characteristics will be summarized descriptively. Categorical variables are reported as counts and percentages. Continuous variables will be summarized as mean ± SD if normally distributed or as median (IQR) if non-normally distributed. Normality will be assessed using the Shapiro–Wilk test.

All analyses will be conducted using SPSS® (version 27, IBM Corp., Armonk, NY, USA) and RStudio (Posit Software, PBC, Boston, USA, version 2025.05.0 + 496). A two-sided *p*-value <0.05 will be considered statistically significant.

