**Objective:**

Primary objective is to assess the association between VET clotting time (CT) in Russell viper venom (RVV) assay and Anti-Xa activity. Secondary objectives include assessing whether VET or Anti-Xa aligns more closely with global haemostatic function, defined by thrombin generation assay (TGA) variables. Exploratory analyses aim to characterise associations among VET parameters, standard laboratory tests, and biomarkers; model dose–exposure–response relationships; and identify clinical modifiers as sepsis or renal dysfunction. Sepsis status will be incorporated as predefined effect modifier in mixed-effects models.

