**Expected results:**

We hypothesize that CT-RVV demonstrates a clinically interpretable monotonic relationship with Anti-Xa activity under ICU conditions. We further anticipate discordance between Anti-Xa and global haemostatic markers in a relevant subset of patients, particularly in sepsis, supporting the hypothesis that VET aligns more closely with functional haemostasis than Anti-Xa alone. These findings are expected to delineate when fixed dosing is insufficient, identify predictors of under- or over-anticoagulation, and guide personalised anticoagulation strategies. If RVV-CT consistently correlates with Anti-Xa across clinical states, VET could streamline monitoring where laboratory turnaround time limits timely dose adjustment; if not, the results will clarify the boundaries of VET applicability and highlight scenarios requiring laboratory confirmation or TGA.

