### Trial objectives

2.1

*Primary objective:* To assess the association between VET and Anti-Xa in critically ill patients with and without sepsis receiving UFH or LMWH, and to evaluate whether VET can serve as a surrogate for Anti-Xa as the reference assay.

*Secondary objective:* To determine whether VET provides complementary or superior information to Anti-Xa activity for characterizing global haemostatic function, as assessed TGA variables, in critically ill patients with and without sepsis.

*Exploratory objective:* To investigate whether extended VET variables and advanced haemostatic biomarkers provide additional information on anticoagulant effects, to explore dose-exposure-response relationships between drug dose, Anti-Xa, VET, and TGA, to assess the influence of patient-level modifiers, and to generate preliminary signals on the predictive value of laboratory profiles for bleeding and thrombotic complications in critically ill patients with and without sepsis.

Given the observational design and sample size, this study is primarily hypothesis-generating. Clinical events, bleeding and thrombosis, are assessed exploratorily and will be interpreted descriptively without claims of definitive prognostic performance.

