### Thrombin generation

2.8

Thrombin generation will be measured using the Innovance® ETP assay (Siemens Healthineers, Marburg, Germany) on an automated coagulation analyser (BCS XP, Siemens Healthineers). Measurements will be performed in platelet-poor plasma. Coagulation will be initiated by addition of tissue factor and phospholipids in the presence of calcium according to manufacturer instructions. Thrombin formation will be quantified via cleavage of a chromogenic substrate, and the increase in optical signal over time will be recorded continuously. The assay software corrects for α2-macroglobulin–bound thrombin activity. From the resulting thrombin generation curve, the following parameters will be derived:

Endogenous thrombin potential (ETP; area under the curve)Peak thrombin generationLag time (time to initiation)Time to peak thrombin generation

Thrombin generation is included as a plasma-based global coagulation assay to complement whole-blood viscoelastic testing and Anti-Xa activity measurements. We acknowledge that PPP-based TGA differs from whole-blood clot dynamics and is sensitive to cellular effects; therefore, TGA results will be interpreted as a complementary plasma-based global readout rather than a direct proxy for whole-blood viscoelastic parameters.

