### Obtained laboratory and patient data

2.10

Primary outcome

1) Variable: VET CT in the RVV test (UFH/LMWH).Metric: Correlation with Anti-Xa activity (for UFH/LMWH); correlation coefficient (Spearman); multivariable mixed-effects regression to account for repeated measures.Aggregation: Point estimates with 95% CI.The time points are as follows: 4 h after the administration of LMWH (expected peak level) or steady-state sampling during continuous UFH infusion.Clinical relevance: Evaluates whether VET-CT can serve as a surrogate for Anti-Xa and assesses its potential as a surrogate monitoring tool.

Secondary outcomes

1) Variable: VET CT in the RVV test (UFH/LMWH); Anti-Xa activity.Metric: Correlation with TGA variables.Aggregation: Spearman correlation coefficients with 95% CIs and regression coefficients for adjusted analyses.Time point: As the primary outcome.Clinical relevance: Examines whether VET provide complementary or superior information to Anti-Xa activity for characterizing global haemostatic function.

Exploratory outcomes

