### Handling for repeated measurements

2.14

All inferential analyses involving repeated measurements will apply mixed-effects modelling with patient-level random intercepts. Simple correlation coefficients are presented for descriptive purposes only.

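### The sole secondary objective asks which assay aligns more closely with thrombin generation, but the plan defines no estimate or confidence interval for the difference between the two correlations

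*Protocol article*

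**What the plan says.** **The question is comparative.** Section 2.1 gives one secondary objective: "To determine whether VET provides complementary or superior information to Anti-Xa activity for characterizing global haemostatic function", with TGA as the yardstick. The abstract puts it as "assessing whether VET or Anti-Xa aligns more closely with global haemostatic function" and, under expected results, states a direction: "supporting the hypothesis that VET aligns more closely with functional haemostasis than Anti-Xa alone". Section 2.10 repeats the aim as the clinical relevance of the secondary outcome: "Examines whether VET provide complementary or superior information to Anti-Xa activity for characterizing global haemostatic function". The Discussion (section 3) words it the same way as the abstract.

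**The analysis is not.** Section 2.10 gives Spearman coefficients with 95% intervals for CT-RVV and Anti-Xa against TGA, plus regression coefficients from adjusted analyses whose model is not described. Section 2.13.3 puts TGA in the family of advanced haemostatic markers and fixes the method: "thrombin generation parameters, PAP, PAI-1, TFPI, TATDescriptive correlation analysesComparative interpretation of effect sizes". Regression is listed for the other two families but not for this one. Change in explained variance is listed only for the standard laboratory assays. Benjamini–Hochberg applies within each family. Section 2.14 adds: "Simple correlation coefficients are presented for descriptive purposes only".

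**Readouts and status.** Section 2.8 derives four TGA readouts: "Endogenous thrombin potential (ETP; area under the curve)Peak thrombin generationLag time (time to initiation)Time to peak thrombin generation". Sections 2.1 and 2.12 call the work hypothesis-generating, and 2.12 states that the TGA analyses have no sample size calculation of their own.

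**The concern.** Superiority of one assay over the other is a statement about a difference between two dependent correlations. Nothing in sections 2.10 or 2.13.3 estimates that difference. Someone following the text would have one coefficient for CT-RVV, one for Anti-Xa, an interval around each, and an instruction to interpret their relative size.

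That invites two errors. A chance gap may be reported as closer alignment of viscoelastic testing, which is the direction the abstract already expects. Or a real gap may be dismissed because two wide intervals overlap. Benjamini–Hochberg helps with neither, because it acts on tests of single correlations against zero and does not compare the assays.

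The complementary part needs a model in which CT-RVV and Anti-Xa stand together. Section 2.10 leaves room for one; section 2.13.3 does not list it.

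**Working it through.** **Plan's own figure.** There is none for this comparison. The pair counts in section 2.12 concern CT-RVV against Anti-Xa and are not used here.

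**Inputs from section 2.12.** Two samples per patient, ICC 0.3, design effect 1 + (2 − 1) × 0.3 = 1.3, 30 LMWH and 36 UFH patients (66). Effective pairs: 66 × 2/1.3 = 101.5; LMWH 30 × 2/1.3 = 46.2; UFH 36 × 2/1.3 = 55.4.

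**Assumed inputs.** Absolute correlations with TGA of 0.4 for one assay and 0.5 or 0.6 for the other. Correlation between the assays 0.6 (the planning value for UFH in 2.12), with 0.3 as a weaker case.

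**Step 1: why separate intervals mislead.** The Meng–Rosenthal–Rubin method for two correlations r1 and r2 sharing one variable, with correlation rx between the assays, gives:

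- m = (r1² + r2²)/2; f = (1 − rx)/(2(1 − m)); h = (1 − f·m)/(1 − m)
- SE of the difference in Fisher z = √(2(1 − rx)h/(n − 3))

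With equal assays (0.4 and 0.4) and rx = 0.6: m = 0.16, f = 0.238, h = 1.145, SE = √(0.8 × 1.145/98.5) = 0.096. Treating the two coefficients as independent gives √(2/98.5) = 0.142. The correct SE is about two thirds of that.

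**Step 2: what side-by-side reading can produce.** On the z scale, a gap of 0.10 centred on 0.4 is atanh 0.45 − atanh 0.35 = 0.119, and 0.119/0.096 = 1.24. Two equal assays would thus differ by 0.10 or more on a single readout in about 22% of studies. In a simulation of equal assays over all four readouts (about 101 pairs, between-assay correlation 0.3–0.6, correlation among readouts 0.5–0.8), at least one readout showed a gap of 0.10 or more in 49–80% of studies, and the readouts named conflicting winners in 43–69%.

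**Step 3: what an interval for the difference can do.** For 0.6 versus 0.4 and rx = 0.6: m = 0.26, f = 0.270, h = 1.256, SE = √(0.8 × 1.256/98.5) = 0.101; (0.693 − 0.424)/0.101 = 2.67; power = Φ(2.67 − 1.96) = 0.76. The same formula gives the other analytic values below. The simulated column is a patient-level bootstrap of the difference in Spearman coefficients (200–250 trials per run, 300 resamples; Monte Carlo SE near 80% is √(0.8 × 0.2/200) = 0.028).

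| Case | Analytic | Simulated |
|---|---|---|
| 66 patients, 0.6 vs 0.4, rx 0.6 | 76% | 76–82% |
| 66 patients, 0.6 vs 0.4, rx 0.3 | 55% | 56–58% |
| 66 patients, 0.5 vs 0.4, rx 0.6 | 25% | 24–25% |
| LMWH only, 0.6 vs 0.4, rx 0.6 | 42% | 44% |
| UFH only, 0.6 vs 0.4, rx 0.6 | 49% | 55–56% |
| 66 patients, equal assays (0.4), rx 0.6 | 5% | 3–6% |

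In the first case the two separate 95% intervals fail to overlap in only 10–15% of trials. With 15% dropout (101.5 × 0.85 = 86.3 pairs) the first analytic value falls to 69%.

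**Step 4: the two sections side by side.** Section 2.10 promises adjusted regression coefficients for CT-RVV and Anti-Xa against TGA. Section 2.13.3 gives TGA descriptive correlation and interpretation only. Both cannot be the full method for the same outcome.

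**The case against.** The strongest defence is the declared status of these analyses. Sections 2.1 and 2.12 call them exploratory and hypothesis-generating, and section 2.8 says TGA is a complementary plasma-based readout, not a direct proxy for whole-blood parameters. A descriptive method suits an exploratory aim. This stands, and it limits the weight of the point. It does not remove the mismatch: sections 2.1 and 2.10 still speak of superior information, and an exploratory estimate still needs to be an estimate of the quantity asked about.

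A reader might infer that the plan cannot address complementary information at all. The text does not support that. The adjusted coefficients in 2.10, together with the mixed models of 2.14, could answer it if both assays enter one model. The article does not say whether they do.

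A reader might also count the four unranked readouts as an error. Section 2.13 refers to a separate analysis plan that is not shown, and a lead readout and covariates may properly be fixed there.

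Nor does any section set a rule based on overlapping intervals. The overlap figure shows only how little the separate intervals reveal.

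Finally, a paired interval is no cure for small numbers. Split by anticoagulant, or for a gap of 0.1, it will often be inconclusive.

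**Conclusion.** The point holds in a limited form. The comparative objective has no comparative estimate: neither 2.10 nor 2.13.3 defines the difference between the two correlations or its interval, and the two sections disagree on whether TGA gets a regression. The superiority wording is unsupported by the stated method; the complementary part is under-specified.

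Under the assumed correlations (between-assay 0.6), a pooled paired interval excludes zero in about 75–80% of trials for a gap of 0.2 and about 25% for a gap of 0.1. Within one anticoagulant it does so in about 45–55% for a gap of 0.2. These figures take complete data, and the TGA correlations are not in the document. The primary analysis is not affected.

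**What to change.** 1. Give the secondary outcome its own analysis, outside the advanced-marker family, so that 2.10 and 2.13.3 agree.
2. Report |ρ(CT-RVV, TGA)| − |ρ(Anti-Xa, TGA)| on samples that have all three values, with a 95% interval from a bootstrap that resamples patients. Absolute values are needed because the amount and time readouts are expected to move in opposite directions. Pool across anticoagulants for the main result; give LMWH and UFH separately as description only. Section 2.13.1 already foresees bootstrap intervals for Spearman coefficients; section 2.14 needs a sentence allowing this one.
3. Fit a mixed model of TGA on Anti-Xa, CT-RVV and anticoagulant type together, with a patient random intercept. Report what each assay adds: standardised coefficient and change in explained variance.
4. Keep the interpretation exploratory, as 2.1 and 2.12 say. Write that one assay is superior or aligns more closely only if the interval of the difference excludes zero; otherwise soften that wording.

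Naming one lead TGA readout is advisable and may be done in the analysis plan.

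The cost is a few sentences and a little more analysis work, with no new samples. The drawback is limited precision, which the report should state.

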### Handling for repeated measurements

2.14

All inferential analyses involving repeated measurements will apply mixed-effects modelling with patient-level random intercepts. Simple correlation coefficients are presented for descriptive purposes only.

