### Sample size

2.12

This study is designed to evaluate the association between Anti-Xa activity and VET variables, with a primary focus on CT in the RVV test, in critically ill patients receiving LMWH or UFH. The planned sample size allows estimation of this association under real-world ICU conditions and supports pre-specified mixed-effects modelling incorporating a limited number of biologically plausible effect modifiers. To account for heterogeneity in coagulation physiology, anticoagulant type (LMWH vs. UFH) and sepsis status will be examined as predefined effect modifiers within the modelling framework. These factors will not be treated as independently powered subgroups but will be analysed using interaction terms. The study is not powered for definitive detection of small correlation coefficients nor for confirmatory subgroup comparisons. Stratified analyses are therefore considered exploratory and hypothesis-generating. Findings will be interpreted cautiously and are intended to inform the design of future adequately powered multicentre studies.

The study is powered for estimation of the Anti-Xa–CT association. Analyses involving thrombin generation are predefined as secondary and exploratory. No separate formal sample size calculation was performed for TGA-CT correlations, as these analyses are hypothesis-generating. The sample size estimation was based on published data reporting a significant Spearman correlation for LMWH-treated patients between Anti-Xa levels and CT-RVV (*r* = 0.669, *p* = 0.0395) (34). For UFH, no exact coefficient was reported, although the same study demonstrated a clear association. For conservative planning, an effect size of *r* = 0.6 was assumed for UFH.

Calculations were performed with G*Power 3.1 (35) for a two-sided test of correlation (*α* = 0.05, power = 0.80). The required sample sizes were 19 independent observation pairs for *r* = 0.669 and 23 pairs for *r* = 0.6. As two temporally separated measurements are planned per patient, the non-independence of repeated measures was adjusted using a design effect with an intraclass correlation coefficient (ICC) of 0.3:

Design−Effect=1+(2−1)×0.3=1.3

$$\text{Effective observations}\;\mathrm{per}\;\text{patient}=\frac{2}{1.3}\approx 1.54$$

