#### Primary analysis

2.13.1

The primary outcome, defined as the correlation between Anti-Xa activity (UFH/LMWH) and CT in the RVV-assay. Because two measurements per patient are planned, the primary inferential analysis will be conducted using a linear mixed-effects model including:

A random intercept for patientA fixed effect for anticoagulant type (UFH vs. LMWH)

This approach accounts for intra-individual correlation and avoids inflation of type I error due to non-independence of repeated observations. Results will be reported as regression slope estimates (per 0.1 IU/mL increase in Anti-Xa activity) with 95% confidence intervals. For descriptive comparability with previous literature, Spearman rank correlation coefficients with bootstrap-derived 95% confidence intervals will additionally be reported:

For the overall cohortStratified by anticoagulant type

Passing–Bablok regression will be applied as a robust method-comparison technique to assess proportional and systematic bias between CT-RVV and Anti-Xa activity (36). Proportional bias will be considered absent if the 95% confidence interval (CI) of the slope includes 1.0, and constant bias absent if the 95% CI of the intercept includes 0.

These criteria are used for methodological characterization rather than to demonstrate assay equivalence. The primary objective is not interchangeability but to determine whether CT-RVV exhibits a stable monotonic relationship with Anti-Xa activity under ICU conditions.

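### The primary outcome is a correlation, but the declared primary analysis is one pooled linear slope, which does not estimate it

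*Protocol article*

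**What the plan says.** All references are to the protocol article.

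- **2.10 (primary outcome).** The variable is CT in the RVV test and the metric is its correlation with Anti-Xa: "correlation coefficient (Spearman); multivariable mixed-effects regression to account for repeated measures". Spearman and regression stand side by side.
- **2.12 (sample size).** The calculation is "for a two-sided test of correlation" at two-sided alpha 0.05 and power 0.80, done separately for LMWH (r = 0.669) and UFH (r = 0.6). The text says the study is powered to estimate the association. It also says that anticoagulant type will be examined as an effect modifier through interaction terms.
- **2.13.1 (primary analysis).** The primary outcome is again defined as the correlation. Then "the primary inferential analysis will be conducted using a linear mixed-effects model including" a random intercept for patient and a fixed effect for anticoagulant type. The reported result is a slope per 0.1 IU/mL with a 95% CI. Spearman coefficients with bootstrap 95% CIs, overall and by type, are added for comparison with the literature.
- **2.14.** "Simple correlation coefficients are presented for descriptive purposes only".
- **Introduction, last paragraph, and end of 2.13.1.** The aim is to learn whether CT-RVV has a stable, monotonic relation to Anti-Xa. A stable correlation would support bedside use of CT; a weak or heterogeneous one would put its advantage in doubt.

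**The concern.** The question asked, the outcome defined and the sample size all concern the strength of a correlation. The analysis that carries inference estimates something else: the mean change in CT per unit of Anti-Xa, assumed linear and common to both drugs. That number depends on the units and says nothing about scatter around the line. It therefore cannot separate the two cases on which the protocol's interpretation turns. It also cannot show whether the relation is monotonic but curved, or whether it differs between LMWH and UFH, because type enters the listed model only as a main effect.

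At stake is how the main result will be read. The headline number would be a slope with its interval. The number that answers the question is labelled descriptive, and the sample size section states neither power nor expected precision for the pooled slope.

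**Working it through.** **1. The plan's own sample size.** Inputs from 2.12: two-sided alpha 0.05, power 0.80, r = 0.669 and 0.6, ICC 0.3, two measurements per patient.

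Fisher z: n = ((1.960 + 0.842)/atanh r)² + 3.
- r = 0.669: (2.802/0.809)² + 3 = 15.0
- r = 0.6: (2.802/0.693)² + 3 = 19.3, rounded up to 20

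The exact bivariate-normal calculation gives 15 and 19. The protocol states 19 and 23, which correspond to power 0.91 and 0.89. The stated pairs do not reproduce by the named method, but they err on the safe side. The next step does reproduce: 19/1.54 = 12.3, so 13 patients, and 23/1.54 = 14.9, so 15. Dropout of 15% alone would give 13/0.85, so 16, and 15/0.85, so 18. The targets of 30 and 36 rest in addition on stable model estimation, for which no figure is given.

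**2. Does the power carry over to the slope?** In a linear model, the test of zero slope and the test of zero Pearson correlation are the same test. A fixed-x slope test with the same r needs 12 and 17 pairs, and has power 0.96 and 0.93 at 19 and 23 pairs. The declared random-intercept model was also simulated (1,500 runs per scenario, ICC 0.3 for both Anti-Xa and residual CT):

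| Patients | True r | Power |
|---|---|---|
| 13 LMWH | 0.669 | 0.98 |
| 15 UFH | 0.6 | 0.95 |
| 28 pooled | 0.669 / 0.6 | above 0.99 |
| 30 + 36 | 0.669 / 0.6 | about 1.00 |
| 30 + 36 | 0.3 in both | 0.94 |
| 25 + 30 (about 15% lost) | 0.3 in both | 0.88 |

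An ICC of 0.6 gives nearly the same values. There is no shortfall.

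**3. What the slope leaves out.** The protocol gives neither a CT slope nor an Anti-Xa SD, so both are assumed here: 10 s per 0.1 IU/mL (100 s per IU/mL) and an SD of 0.15 to 0.35 IU/mL. The explained SD is 100 × SD, and the residual SD is the explained SD × √(1/r² − 1).

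| Anti-Xa SD | Explained SD | Residual SD, r = 0.3 | Residual SD, r = 0.8 |
|---|---|---|---|
| 0.15 | 15 s | 48 s | 11 s |
| 0.25 | 25 s | 79 s | 19 s |
| 0.35 | 35 s | 111 s | 26 s |

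The slope is identical in every cell. The ratio between the last two columns is 3.18/0.75 = 4.2, whatever slope and SD are assumed.

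**4. What the correlation would deliver.** By the protocol's own count, the effective observations are 30 × 2/1.3 = 46 (LMWH), 36 × 2/1.3 = 55 (UFH) and 66 × 2/1.3 = 101 (overall). Approximate 95% CI for Spearman: tanh(atanh r ± 1.96 × √((1 + r²/2)/(n − 3))).
- LMWH, r = 0.669, n = 46: standard error 0.169, CI 0.44 to 0.81
- UFH, r = 0.6, n = 55: standard error 0.151, CI 0.38 to 0.76
- Overall, r = 0.3, n = 101: standard error 0.103, CI 0.11 to 0.47

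The last interval excludes zero, yet 0.3² is only 9% of variance. A result of that kind is informative when read as an estimate with its interval, and not when read as a test against zero.

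**The case against.** The best defence is that nothing is lost. Section 2.10 lists mixed-effects regression beside Spearman, so the slope was not brought in unannounced, and 2.13.1 gives a sound reason for it: two measurements from one patient are not independent. Spearman coefficients with bootstrap CIs are already promised overall and by drug. The study calls itself mainly hypothesis-generating.

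Most of this stands, and it rules out three stronger readings that a reader might infer.

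- *The 80% power does not apply to the primary analysis, or the study is underpowered.* Not supported. The two tests are nearly equivalent, the design effect deals with the pairing, and the model exceeds 80% under the protocol's inputs.
- *A significant slope will count as success.* No section sets such a rule, and the introduction ties the conclusion to the correlation. Nor would a correlation tested against zero be any safer: at r = 0.3 and 101 effective observations it would be significant with probability Φ(0.3095 × √98 − 1.96) = 0.87.
- *A weak correlation would stay hidden.* It would be reported, with an interval.

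The defence does not remove the mismatch itself. Listing both metrics in 2.10 leaves open which is primary. Section 2.13.1 then defines the outcome as one and rests inference on the other. Non-independence does not force that choice, because a bootstrap that resamples patients handles it for a rank correlation too.

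**Conclusion.** The point holds as an inconsistency between the defined primary outcome and the declared primary analysis. The pooled slope does not measure the strength, monotonicity or stability of the relation on which the protocol says its conclusion will depend, and no power or precision is stated for it. The effect is on what the headline result means, not on the chance of detecting an association.

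The finding that power is adequate rests on assumptions outside the protocol: normal data, a linear relation, equal variances within drug, and an ICC of 0.3 (checked at 0.6) applied to both Anti-Xa and residual CT. The 4.2-fold difference in scatter follows from r alone and needs none of the assumed slope or SD values. The intervals in step 4 are approximations based on the protocol's effective-observation count. It is worth settling before database lock, because both statistics are already planned.

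**What to change.** Make the Spearman coefficient, per drug and overall, the primary estimate, with a 95% CI from a bootstrap that resamples patients and keeps both measurements of a patient together. Say that it will be judged on its size and interval, not on significance against zero. The per-drug coefficients match the sizing in 2.12; the overall one also takes in differences between the drugs. Keep the mixed-model slope, with its residual SD, as the supporting analysis. Name Spearman alone as the primary metric in 2.10, amend 2.13.1 and 2.14 to match, and state in 2.12 the expected interval width for the coefficient.

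If the slope is to stay primary, change the outcome definition in 2.10 and 2.13.1 to a slope, and restate power or expected CI width in 2.12 for the pooled model. Also say whether a type-by-Anti-Xa interaction belongs to that model, since 2.12 announces one and 2.13.1 does not list it.

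Cost: wording in 2.10 to 2.14, with no new data or assays. The patient-level bootstrap interval may be somewhat wider than one that ignores the pairing.
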